# The 5x1 DAFNE study protocol: a cluster randomised trial comparing a standard 5 day DAFNE course delivered over 1 week against DAFNE training delivered over 1 day a week for 5 consecutive weeks

**DOI:** 10.1186/1472-6823-12-28

**Published:** 2012-11-08

**Keywords:** Type 1 diabetes, Education, Teaching, Training programs

## Abstract

**Background:**

Structured education programmes are now established as an essential component to assist effective self-management of diabetes. In the case of Type 1 diabetes, the Dose Adjustment For Normal Eating (DAFNE) programme improves both glycaemic control and quality of life. Traditionally delivered over five consecutive days, this format has been cited as a barrier to participation by some patients, such as those who work full-time. Some centres in the UK have organised structured education programmes to be delivered one day a week over several consecutive weeks. This type of format may add benefit by allowing more time in which to practice skills between sessions, but may suffer as a result of weaker peer support being generated compared to that formed over five consecutive days.

**Methods/design:**

We aim to compare DAFNE delivered over five consecutive days (1 week course) with DAFNE delivered one day a week over five weeks (5 week course) in a randomised controlled trial. A total of 213 patients were randomised to attend either a 1 week or a 5 week course delivered in seven participating centres. Study outcomes (measured at baseline, 6 and 12 months post-course) include HbA_1c_, weight, self-reported rates of severe hypoglycaemia, psychosocial measures of quality of life, and cost-effectiveness. Generalisability was optimised by recruiting patients from DAFNE waiting lists at each centre, and by mailing eligible patients from hospital clinic lists. The inclusion and exclusion criteria were identical to those used to recruit to a standard DAFNE course (e.g., HbA_1c_ <12%, with no lower limit). Qualitative interviews were undertaken with a sub-sample of n=30 patients and their course educators (n=11) to help understand and interpret differences and similarities in outcomes between the 
two arms, and to identify logistical problems and unanticipated issues arising from the adaptation and delivery of 
a 5 week course.

**Discussion:**

This trial has been designed to test the hypothesis that the benefits of delivering a structured education programme over 5 weeks are comparable to those observed after a 1 week course. The results of the trial and the qualitative sub-study will both inform the design and delivery of future DAFNE courses, and the development of structured education programmes in other fields of medicine.

**Trial Registration:**

Clinicaltrials.gov NCT01069393

## Background

The DAFNE (Dose Adjustment for Normal Eating) course is a 1 week structured education course teaching skills in insulin use and dietary freedom to individuals with Type 1 diabetes, which was originally adapted from a German inpatient programme [1]. The original DAFNE trial, published in 2002, demonstrated that a dose adjustment for normal eating approach led to improved glycaemic control and quality of life without increases in severe hypoglycaemia, benefits which lasted for at least 1 year [2]. DAFNE is now a nationally and internationally delivered evidence-based, quality assured programme [3], delivered in 76 centres across the UK and as well as in Ireland, Australia (Oz DAFNE), New Zealand, Kuwait and Singapore.

The development of structured education programmes, such as DAFNE has had a major impact on the treatment of Type 1 diabetes in the UK. The Department of Health [4] now requires structured education programmes to be offered to all individuals with Type 1 diabetes in England and Wales, and most secondary care centres offer some form of skills training to adults with Type 1 diabetes. However, the format of non-DAFNE programmes currently offered to patients varies widely in terms of duration, number of sessions, level of quality control and designs are not evidence based. It has been suggested that it may not always be easy for some people to find the time to attend an intensive 1 week course, patients cite difficulties due to work obligations or arranging child-care. This may, in part, explain the observation that around 50% of adults with Type 1 diabetes attending centres which run DAFNE training have not yet received this type of education. Meanwhile, many non-DAFNE structured education courses are delivered on a one day a week basis for between 2 and 8 weeks [5] which may have improved access, although in the absence of any definitive data this is hypothetical. There has been one randomised control trial examining the effect of a shorter period of structured education (2.5 days) over 6 weeks in a single centre, but no improvements in biomedical outcomes were observed [6].

Some non-DAFNE centres have reported outcomes during routine care in self-selected individuals which are comparable to those reported in the original DAFNE trial [7]. Yet, since observational data of this type are prone to bias it is unclear whether such an extended approach to skills training is as effective as that provided on a 1 week intensive course. This randomised control trial is designed to test the hypothesis that the benefit of a structured education programme, with the identical contact time, is the same whether delivered over 1 or 5 weeks.

There are theoretical reasons why the two approaches might lead to different outcomes. A 1 week model might lead to stronger peer support developing over the week that could help to improve incorporation of self-management skills. Alternatively, a course delivered over 5 weeks might allow patients to gain more practice in self-management skills during the weeks between education sessions, thus facilitating integration of its principles into everyday life, and hence enhance sustainability. However, the potentially weaker peer support on a 5 week course may lead to a higher drop-out rate, with less participants completing the full 5 days of skills training.

Establishing whether DAFNE delivered at weekly intervals is as effective as delivering it over 5 consecutive days will help guide and inform decisions about future course delivery. Potentially it could also allow more individuals with Type 1 diabetes to receive structured education and increase patient choice. As qualitative work can provide important insights into trial outcomes [8], a qualitative sub-study was conducted in which we drew upon people’s understandings and experiences, by interviewing both educators and course participants. We also surveyed participants at the end of the trial asking whether they would prefer future structured education programmes to be delivered over 1 week or a more extended period of 5 weeks. Included in this survey were questions enquiring as to current self-management strategies.

## Methods/design

The DAFNE 5x1 day RCT is a multi-centre randomised trial comparing 2 different methods of delivering the DAFNE programme in the UK.

The objectives:

1) To explore whether the outcomes of a structured education programme with identical contact time are comparable whether delivered over 1 or 5 weeks.

2) To examine the cost effectiveness of a DAFNE course delivered either over 1 or 5 weeks.

3) To calculate how many patients choose to receive structured education programmes over 1 or 5 weeks, by conducting a preference survey.

4) The aims of the qualitative sub-study were

a) Help understand and interpret any differences and similarities in biomedical and psychological outcomes between patients attending DAFNE courses delivered over 1 or 5 weeks.

b) Identify any logistical problems and unanticipated issues arising from the adaptation and delivery of DAFNE as a course spread over 5 weeks.

5) Provide recommendations for the timing, content and delivery of future DAFNE courses.

Ethical approval was obtained from the Derbyshire Research Ethics Committee (09/H0401/91). Written informed consent was obtained from all trial participants, after they had had sufficient time to consider the Patient Information Sheet and had any questions pertaining to the trial answered. Additional written informed consent was obtained from participants in the qualitative sub-study. The study is registered with the local Research and Development department of each study centre and Sheffield Teaching Hospitals NHS Foundation Trust is acting as the sponsor.

Funding was secured as part of a NIHR programme grant for applied research – Improving management of Type 1 diabetes in the UK: the DAFNE programme as a research test-bed (application number RP-PG-0606-1184).

### Recruitment procedures

Secondary care centres with experience in delivering high quality structured education using DAFNE participated in the trial. When invited in 2009, seven out of a possible 74 DAFNE centres volunteered to take part. All eligible participants on the DAFNE waiting list received a written invitation to join the study from their local diabetes team. After indicating initial interest they were contacted by a member of the local research team or educator who provided further information, which, in some centres, included an invitation to an information evening, prior to obtaining informed consent. Participants were informed of a pair of course dates (a one week and a 5 week course) for which they would need to be available. After obtaining consent, the participants were randomised to either attend one or other format of course, i.e., either a 1 week or 5 week course. Recruitment took place between May 2010 and April 2011. When consent was obtained, patients were also asked to indicate whether their contact details could be made available to the qualitative research team in order that they might be approached to take part in the qualitative sub-study. Those who were approached were given further written information about the qualitative study and asked to opt-in using a separate consent form.

The *inclusion criteria* were as follows: Adults with Type 1 diabetes for at least 6 months, aged 18 – 80 y, HbA_1c_ <12%, willing to undertake intensive insulin therapy, with multiple self-monitoring of blood glucose (SMBG), carbohydrate counting, insulin self-adjustment and no strong views on attending a 1 week course or a 5 week course. Participants needed to agree to randomisation regardless of preference, having not yet completed DAFNE training or equivalent.

The *exclusion criteria* were as follows: severe diabetic complications (these include renal replacement therapy, severely impaired vision), inability to communicate in English, strong preference for either a 1 week or a 5 week course, severe needle phobia, unenthusiastic about undertaking SMBG and insulin self-adjustment, or inability to give informed consent.

### Sample size

Using a non-inferiority design, and based on clinically relevant difference of HbA_1c_ of 0.5%, a standard deviation of 1.5 and groups of 7–8 participants per randomisation group, for 80% power at one-sided 5% significance 150 participants were required to complete the study procedures. Allowing for a 10% drop-out from randomisation to completion of the trial, it was anticipated that we would require 166 subjects to be randomised in the study. Thus we aimed to run 24 courses (12 courses per arm). Each centre was required to recruit 32 patients to enable 4 courses (two standard DAFNE and two 5 week) to be run with 8 participants on each. However, during the recruitment phase of the trial it became apparent that the drop-out rate between randomisation and course participation was higher than had been anticipated, at over 11%, hence one centre ran an extra pair of courses.

The flow of patients through the trial is shown in Figure 1, this figure follows the CONSORT approach, as will future reporting of the trial results [9].

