### Analysis

The primary analysis will be a linear model of HbA_1c_ at 12 months with baseline HbA_1c_ as a covariate, (which will improve the power relative to the predicted power), using generalised estimating equations (GEE) to control for clustering within courses. The intracluster correlation coefficient coefficient (ICC) will be estimated using the method of moments. Poisson regression (or a zero-inflated Poisson regression if necessary) will be used on the number of hypoglycaemic episodes over 12 months, which should also have more power than a dichotomy of having/not experiencing an episode, again using GEE to account for clustering. We will use an intention to treat analysis, but will explore the issue of participants dropping out using multiple imputations. The full analysis set (FAS) for the intention to treat analysis includes all patients for whom baseline data was collected. A per protocol analysis will also be performed.

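### On the inputs stated for it, the target of 150 completers gives about 65% power, not 80%; 80% needs about 223 before any allowance for course clustering

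*Protocol article*

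**What the plan says.** The Sample size section describes a non-inferiority design "based on clinically relevant difference of HbA_1c_ of 0.5%, a standard deviation of 1.5", with groups of 7–8, and concludes that "for 80% power at one-sided 5% significance 150 participants were required to complete the study procedures". The next step takes the 150 as given: "Allowing for a 10% drop-out from randomisation to completion of the trial, it was anticipated that we would require 166 subjects to be randomised". The 150 is therefore a total over both arms, to be reached through 24 courses, 12 per arm.

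The Analysis section sets the primary analysis as a linear model of 12-month HbA1c with baseline HbA1c as a covariate, using GEE for clustering within courses. It says of the covariate "which will improve the power relative to the predicted power". The Outcomes section defines the primary outcome as change from baseline at 6 and 12 months, and says that repeated measures improve power. The article gives no planning ICC, no baseline to follow-up correlation, and no correlation between the two follow-ups. The Abstract reports 213 randomised.

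**The concern.** The article prints a margin, a standard deviation, a one-sided alpha, a power and a sample size. The first four determine the fifth, and the printed fifth is about a third too small. Two features of the plan might be thought to explain a smaller number, but neither does. Clustering moves the requirement up, not down. The gain from baseline adjustment is, in the plan's own words, on top of the prediction.

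What is at stake is the reading of the result. If the confidence limit for the difference crosses 0.5%, a reader will weigh that outcome against a design said to have 80% power. On the stated inputs the figure is nearer two in three. The target of 166 to be randomised inherits the same problem, because it is 150 with a drop-out allowance.

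**Working it through.** **Inputs (Sample size section unless noted).** Margin 0.5% HbA1c; SD 1.5; one-sided alpha 5% (z = 1.645); power 80% (z = 0.842); 150 completers in total, 75 per arm. The true difference is not stated and is taken as 0, the usual choice for non-inferiority.

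**Attempt to reproduce 150.**

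- n per arm = 2 × (1.645 + 0.842)² × (1.5/0.5)² = 111.3.
- Total = 222.6, about 223 (224 if each arm is rounded up). Stated: 150.

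**Power at 150.**

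- SE = 1.5 × √(2/75) = 0.245.
- 0.5/0.245 − 1.645 = 0.396, so power = 65.4% (65.1% with the noncentral t). Stated: 80%.

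**Other readings of the stated inputs.**

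| Reading | Result |
|---|---|
| One-sided 2.5% | 284 needed |
| 90% power, one-sided 5% | 310 needed |
| Equivalence by two one-sided tests | 31% power at 150 |
| 150 per arm | 89% power, but incompatible with 166 randomised |

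None returns 150 at 80%.

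**Clustering.** The design effect is 1 + (m − 1) × ICC. Here m = 7.5 is the midpoint of the stated 7–8, and the ICC values are assumptions.

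| ICC | Design effect | Power at 150 | Completers for 80% |
|---|---|---|---|
| 0 | 1.000 | 65% | 223 |
| 0.02 | 1.130 | 61% | 252 |
| 0.05 | 1.325 | 55% | 295 |
| 0.10 | 1.650 | 48% | 367 |

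**What would make 150 right with no clustering.** Any one of these would do; the article states none of them:

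- an SD of 1.23 in place of 1.5;
- a margin of 0.61 in place of 0.5;
- a baseline correlation r with 1 − r² = 150/222.6, so r = 0.57;
- the mean of two follow-ups correlated at 0.35, from (1 + ρ)/2 = 150/222.6;
- a change score with SD 1.5 × √(2(1 − r)), which gives 1.23 at r = 0.66.

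**Power of the planned analysis for the trial as recruited.** Baseline adjustment multiplies the variance by (1 − r²) and clustering by the design effect. Completers at 12 months, r and ICC are all assumptions.

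| Completers | ICC | r | Power |
|---|---|---|---|
| 190 | 0 | unadjusted | 74% |
| 190 | 0.05 | unadjusted | 64% |
| 170 | 0.05 | 0.5 | 70% |
| 170 | 0.05 | 0.6 | 76% |
| 190 | 0.05 | 0.6 | 80% |

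For example, with 190, ICC 0.05 and r = 0.6: SE = 1.5 × √(4/190 × 1.325 × 0.64) = 0.200; 0.5/0.200 − 1.645 = 0.85; power 80%.

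The 190 is 213 × 0.89. The loss of over 11% in the Sample size section runs only from randomisation to course participation, so 190 is close to an upper limit on those who started a course. The number with a 12-month HbA1c is not known from the text.

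**The case against.** The best defence is that an input was used but not printed. The Outcomes section defines the primary outcome as change from baseline. If 1.5 is a cross-sectional SD and the calculation was done on change scores, 150 follows at r = 0.66 with no clustering, or very nearly (150.9) at r = 0.70 with ICC 0.02 and 7.5 per course. A covariate-adjusted model would still improve on that prediction, so the remark in the Analysis section would remain true. The full protocol, which is not shown, may hold such an input. This stands as far as it goes: a reader should not infer that 150 is irreproducible under every assumption, only that it does not follow from what is stated. It does not rescue the text, which gives an SD of 1.5 and no correlation. The repeated-measures route is weaker still, since the primary analysis uses the 12-month value.

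A second defence is that the trial may have adequate power in practice. It randomised 213 against a target of 166, and the planned analysis adjusts for baseline. This also stands: a reader might infer from the 65% that the trial is underpowered, but the documents do not support that, because the power of the planned analysis depends on an r and an ICC that they do not give. Nor do they support the opposite assurance. The 80% at 190 completers is one favourable combination of three assumed values.

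Third, the consequences are limited. The 0.5% margin is an input and does not rest on the 150, and the extra pair of courses is attributed to drop-out. Both points are correct.

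**Conclusion.** The statement is wrong as written. On a margin of 0.5% HbA1c, SD 1.5, one-sided 5% and a true difference of 0, 150 completers give about 65% power, some 15 points below the stated 80%. Reaching 80% needs about 223, so 150 is roughly two thirds of the requirement. This rests only on printed inputs and the usual zero-difference assumption. That clustering makes the shortfall larger is certain for any positive ICC; by how much depends on an assumed ICC. Over-recruitment narrows the gap without closing it on the unadjusted calculation: even all 213 with no loss and no clustering give 78%.

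The conclusion concerns the stated calculation, not the achieved power of the baseline-adjusted analysis, which cannot be fixed from the documents. It matters for interpreting an inconclusive non-inferiority result. It leaves the margin and the analysis as they are.

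**What to change.** Withdraw the claim that 150 completers give 80% power. Either name the input that produced 150 (for instance a change-score SD or a repeated-measures correlation, with its value and source), or state that 150 gives about 65% on the printed inputs before clustering.

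Then report the power of the planned 12-month analysis, adjusted for baseline and clustered by course, for the 12-month completers expected from the 213 randomised. Give it as a range, with the assumed completers, completers per course, ICC and baseline correlation each labelled as assumptions. The last table in the working shows the form; no single row should be quoted alone.

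The cost is one rewritten paragraph, carried into the report of results, and a less favourable figure for 150. Recruitment closed in April 2011 and no added enrolment is asked for.

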**Figure 1 F1:**
[figure not shown]
Flow diagram of the participant progress through the phases of the 5x1 randomised control trial.

### Randomisation

After consent and completion of baseline data collection, the participants were individually randomised using a random block size, stratified by centre and a web-based remote randomisation system into either a 1 week course or a 5 week course. The allocation sequence was generated by [name] using a computer program called RANDOLOG (University of Southampton). The centres sent a list of participant study numbers to CE, the project manager, who performed the blinded randomisation and informed the centres of the results.

### The intervention

Patients were randomised to either:

• 1 week - The standard DAFNE 1 week course, or

• 5 weeks - The DAFNE course delivered on one day a week over 5 consecutive weeks

Although pragmatic in design, in order to try to reduce bias, each Centre’s 1 week and 5 week courses were delivered by the same two DAFNE educators, so that the skills, enthusiasm or teaching style of an educator did not favour one arm over the other. As defined for standard DAFNE courses, a participant was deemed to have completed the course if they attended for at least 4 full days of the 5 day course. Where a participant missed a day, attempts were made by the educators to cover missed material on an individual basis also as per normal DAFNE procedures. If a course could not be filled with trial participants, individuals undergoing DAFNE training but not consented to the trial (‘fillers)’ were included so as to maintain the normal dynamics of DAFNE group education.

### 1 week - The standard DAFNE 1 week DAFNE course

Each course took place over five consecutive days and was delivered to groups of 5–8 adults. The curriculum uses a progressive modular based structure to improve self-management in a variety of medical and social situations. The curriculum is designed to deliver key learning topics at the appropriate time within the programme. In this way, knowledge and skills are built up throughout the week with active participant involvement and problem solving as key methods of learning. The key modules are: what is diabetes; food and diabetes; insulin management; management of hypoglycaemia; sick day rules. Learning objectives for each day and each session are clearly identified and educators have instructions on session preparation and teaching materials. Lesson plans give guidance on timing and a student activity section serves to give an idea of expected responses. Each meal and snack is used as an opportunity to practise carbohydrate estimation and insulin dose adjustment.

### 5 weeks - The DAFNE course delivered on one day a week over 5 consecutive weeks

The curriculum was adapted from the standard course described above. This process was informed by qualitative interviews performed during an earlier mixed methods study of the DAFNE programme, in which patient and educator views were solicited as to how the curriculum could be adapted for a 5 week course. Four experienced DAFNE educators met with the qualitative researchers to exchange ideas and then further refinements were communicated within the group via e-mail. The contents of the two curricula were identical in terms of educational content and skills training although we made some minor changes to accommodate the needs of those attending over 5 weeks. Thus rather than providing a workbook on each day of the course, those attending 1 week courses received an entire workbook at the outset. The hope was that this would encourage participants to attend each week to gain more information and thereby reduce the drop-out rate. Also, blood glucose diaries were modified to allow for additional space to record to events / physical activity in more detail. The adapted curriculum was tested in 3 pilot courses, at 2 different centres, prior to commencement of the main trial. As a result of the pilot courses minor modifications were made to two of the sessions.

